# Evaluating the therapeutic efficacy of the Chinese herbal medicine Yishen Tongbi decoction in patients with active rheumatoid arthritis: protocol for a randomized, controlled, noninferiority trial

**DOI:** 10.1186/s13063-019-4005-0

**Published:** 2019-12-30

**Keywords:** Yishen Tongbi decoction, Rheumatoid arthritis, Efficacy, Methotrexate, Double-blind, Prospective, Randomized controlled, Traditional Chinese medicine

## Abstract

**Background:**

Rheumatoid arthritis (RA) is a common chronic autoimmune disease that seriously affects the quality of life of patients because of damage to joints. Presently, RA is mainly treated with disease-modifying antirheumatic drugs (DMARDs) or biological agents; however, they offer limited efficacy in some patients. Therefore, additional therapeutic strategies need to be developed. Yishen Tongbi decoction is a traditional Chinese medicine formulation widely used to treat RA in China. However, currently, there is insufficient evidence to recommend its use for the treatment of RA. Therefore, we aim to verify the efficacy of Yishen Tongbi decoction to treat RA by a noninferiority trial, and to provide a basis for its use with a full-scale clinical trial.

**Methods/design:**

One hundred eligible patients with RA will be randomized into two groups of 50 patients. One group will receive Yishen Tongbi decoction and placebo replacing methotrexate (MTX), while the other group will receive MTX and placebo replacing Yishen Tongbi decoction. Patient’s whose visual analogue scale score for pain is greater than 40 mm will be administered nonsteroidal anti-inflammatory drugs (such as enteric-coated diclofenac sodium, 25 mg three times a day); administration of all medications will be recorded. The clinical indicators of patients and their disease activity will be assessed at baseline and at 4, 12 and 24 weeks after treatment initiation. The primary outcome of efficacy will be the proportion of patients who demonstrate a favourable response based on their Clinical Disease Activity Index score at 24 weeks after treatment. All adverse events will be reported.

**Discussion:**

Traditional Chinese medicine theory and modern western medicine research have identified the efficacy of Yishen Tongbi decoction to treat RA. Previous clinical observation and efficacy trials of Yishen Tongbi decoction in animal models for the treatment of RA has demonstrated significant effect. Because of the potential benefits of Yishen Tongbi decoction in the treatment of patients with RA, we designed this double-blind, prospective, randomized controlled trial; the results and conclusions of the trail will be published after the completion of the study.

**Trial registration:**

Chinese Clinical Trials Registry, ChiCTR1900024902. Registered on 3 August 2019.

## Background

Rheumatoid arthritis (RA) is a chronic autoimmune disease that progressively destroys joints and negatively influences other physiological areas and aspects, such as the blood vessels and metabolism. RA affects 1% of the global population, and may occur at any age, with women often being more susceptible to developing RA than men [1]. RA is a chronic disease, and affected individuals need regular treatment for prolonged durations which puts a heavy burden on them [2]. RA not only increases the medical expenses of affected individuals but also leads to functional disability, reduces their ability to work and creates a socioeconomic burden [3]. Therefore, early diagnosis, prompt treatment, and development of new treatment modalities to control inflammation and prevent additional damage is warranted in cases of RA [4].

Disease-modifying antirheumatic drugs (DMARDs) remain the most commonly used therapeutics for RA, and the use of methotrexate (MTX) is preferred over other DMARDs [5]. DMARDs have a limited role in preventing the progression of RA and have potential risks, including infection, malignancy, and production of autoantibodies. Therefore, it is necessary to develop newer antirheumatic drugs with higher efficiency and lower toxicity [6].

Yishen Tongbi decoction is a traditional Chinese medicine (TCM) formulation widely used to treat RA in China. This TCM decoction is made from *Fructus Ligustri Lucidi*, *Herba ecliptae*, *Eucommia ulmoides Oliver*, *Fructus lycii*, *Salvia miltiorrhiza Bge*, and *Tripterygium hypoglaucum (Levl.) Hutch.* In China, *Tripterygium hypoglaucum (Levl.) Hutch* is widely used as a TCM for the treatment of RA. Kunmingshanhaitang tablets which are extracted from *Tripterygium hypoglaucum (Levl.) Hutch* are approved for the treatment of RA by Chinese Pharmacopoeia.

We previously examined the efficacy of Yishen Tongbi decoction on an animal model of RA. The results showed that, compared with MTX alone, *Tripterygium hypoglaucum (Levl.) Hutch* alone, and several other TCM compounds, Yishen Tongbi decoction demonstrated a better effect in improving inflammation, inhibiting synovial hyperplasia, and inhibiting joint destruction [7].

Additionally, we conducted a clinical observational study on the use of Yishen Tongbi decoction to treat RA. By comparing the disease activity and clinical indicators of 30 patients with active RA before and after treatment with Yishen Tongbi decoction, we observed significant improvement in clinical symptoms, inflammation index, and disease activity after treatment with Yishen Tongbi decoction [7].

Thus far there has been little research on the effectiveness of TCM decoction in the treatment of RA. Through this clinical study, we aim to explore the efficacy of Yishen Tongbi decoction in the treatment of active RA and to compare the efficacy of Yishen Tongbi decoction and MTX.

We designed this study as a double-blind, prospective, randomized controlled trial. Our research plan and informed consent were submitted to the Ethics Committee of the First Clinical Medical College of Guangzhou University of Traditional Chinese Medicine in November 2018. After two revisions, ethical approval was obtained on 10 April 2019. The results will be released after the trial is completed.

## Methods

### Study design

This study is a double-blind, randomized controlled, noninferiority trial. One hundred eligible patients with RA will be randomized into two groups of 50 patients. One group will receive Yishen Tongbi decoction and placebo replacing MTX, while the other group will receive MTX and placebo replacing Yishen Tongbi decoction. The study protocol has been approved by the Ethics Committee of the First Affiliated Hospital of Guangzhou University of Traditional Chinese Medicine (approval number ZYYECK-2018-141) and registered with the Chinese Clinical Trial Registry (ChiCTR-1,900,024,902). The study flowchart is shown in Fig. 1. The Standard Protocol Items: Recommendations for Interventional Trials (SPIRIT) checklist is presented in Additional file 1, and the SPIRIT figure is shown in Fig. 2.

**Fig. 1 Fig1:**
[figure not shown]
Study flowchart. MTX methotrexate

**Fig. 2 Fig2:**
[figure not shown]
SPIRIT figure showing time points for enrolment, interventions and assessment. *Laboratory examination includes complete blood count, rheumatoid factor, Anticyclic citrullinated peptide antibody, C-reactive protein, erythrocyte sedimentation rate, liver function tests (aspartate aminotransferase, alanine aminotransferase) and renal function (creatinine, urea). ACR20/50/70 improvement in American College of Rheumatology criteria of 20%/50%/70%, CDAI Clinical Disease Activity Index, DAS28 Disease Activity Score in 28 joints, MTX methotrexate, SDAI Simplified Disease Activity Index

### Inclusion criteria

Subjects must meet all of the following requirements:
Meet the 2010 American College of Rheumatology (ACR)/European League against Rheumatism classification criteria and must have active RA for at least 6 weeksBe 18–65 years of ageHave at least three swollen joints and five tender jointsHave C-reactive protein >20 mg/L or erythrocyte sedimentation rate >28 mm/hProvide signed informed consent form

### Exclusion criteria

Subject who do not meet any of the following will be excluded:
Pregnant or lactating womenFertility requirements at present or in the futureHistory of severe chronic infection, current infection, and malignant tumourPatients with severe primary diseases, such as those of the cardiovascular, cerebrovascular, hepatic, renal, and hematopoietic systems, and mental illness.White blood cell count <3.5 × 10^9^/L, haemoglobin <100 g/L, alanine aminotransferase or aspartate aminotransferase ≥1.5 times the upper limit of normal, serum creatinine greater than the upper limit of normalHistory of drug allergyUse of DMARDs or other biological agents within the first 3 months of enrolmentThe investigator believes that it is not appropriate for the patient to participate in this clinical trial

### Randomization and blinding

A random sequence of 100 participants from the First Affiliated Hospital of Guangzhou University of Chinese Medicine was generated by computer software (Excel) and, thereafter, segmented randomly. We set 25 blocks, each of which included four participants. Two participants of the four were randomly assigned to the Chinese medicine group and two to the western medicine group. The blinded results are kept opaque envelopes; one is kept by the research sponsor and the other by the pharmacy leader. Both researchers and patients are blinded to the grouping. Unblinding will be carried out before the statistical analysis, which will be performed by the Professor of Statistics of Guangzhou University of Traditional Chinese Medicine who will also supervise the scene and report the unblinding time, the compliance with the regulations, and the acceptability of the sealed envelopes in the statistical report.

### Interventions

For the TCM (Yishen Tongbi decoction), a dose decoction made from *Fructus Ligustri Lucidi* 15 g, *Herba ecliptae* 15 g, *Eucommia ulmoides Oliver* 15 g, *Fructus lycii* 15 g, *Salvia miltiorrhiza Bge* 15 g, *and Tripterygium hypoglaucum (Levl.) Hutch* 25 g will be used.

For the western medicine, MTX tablets are provided by Shanghai Xinyi Pharmaceutical Co., Ltd.

For the TCM replacement of Yishen Tongbi decoction with placebo, 300 doses of decoctions will be made from water 4.5 L, maltodextrin 200 g, caramel colouring 35 g, sucrose octa-acetate 1.6 g, and liquorice essence 9 g.

For the placebo to replace MTX, 700,000 tablets will be made from Titanium Aluminium Lake 0.607 kg, corn starch 37.8 kg, sucrose 16.8 kg, dextrin 1.68 kg, and magnesium stearate 0.56 kg.

Patients in the Chinese medicine therapy group will be given Yishen Tongbi decoction (150 mL once a day) along with placebo for MTX (starting from 7.5 mg once a week, increasing to 15 mg once a week within 4 weeks). Participants in the western medicine group will be given MTX (starting from 7.5 mg once a week, increasing to 15 mg once a week within 4 weeks) along with placebo for Yishen Tongbi decoction (150 mL once a day). The entire treatment process will last for 24 weeks.

Folic acid tablets (10 mg) will be administered the day after every MTX (or placebo for MTX) treatment. Systematic evaluation shows that the folic acid supplementation during methotrexate treatment can reduce the adverse reactions, such as gastrointestinal side effects and liver damage [8].

Nonsteroidal anti-inflammatory drugs (diclofenac sodium as enteric-coated tablets, 25 mg three times a day) may be added if necessary (for patients with visual analogue scale score for pain ≥40 mm) during the treatment, and such events will be recorded. Treatment can be maintained if the patient has taken a steady dose of a corticosteroid or a nonsteroidal anti-inflammatory drug before the trial. Participants’ medication information will be recorded in the case report form (CRF) at each follow-up visit.

### Outcomes and measurements

This is a double-blind study where neither the researcher nor the patient is aware of the groupings. The investigators will collect the clinical data and assess disease activity at baseline and at 4, 12 and 24 weeks after treatment initiation. Adverse events will be reported in a timely manner.

The primary outcome of efficacy is the proportion of patients who achieve a result of good response on the Clinical Disease Activity Index (CDAI; defined as achieving ≥50% improvement in the CDAI or CDAI ≤2.8) at 24 weeks [9–12].

Secondary outcomes of efficacy are the proportion of patients achieving a result of good response on the Simplified Disease Activity Index (SDAI; defined as achieving ≥50% improvement in the SDAI or SDAI ≤3.3), and those achieving a 20%, 50% and 70% improvement in the ACR criteria (ACR20, ACR50 and ACR70, respectively) at 24 weeks.

### Safety outcomes

At baseline and at each study visit, safety checks will be performed on the patients by evaluating their complete blood count (CBC), aspartate aminotransferase, alanine aminotransferase, creatinine, and urea levels. We will compare the safety of traditional Chinese and western medicines by comparing the abnormalities among the safety indicators of the two groups.

### Adverse event reporting

An adverse event (AE) is the presence or worsening of any syndrome, symptom or disease that occurs in a patient during the clinical trial and which affects the patients’ health. The term AE does not imply a causal relationship with a test drug. The investigators will record the AEs in a timely manner, and signed and dated reports will be submitted to the sponsors, ethics committees, and drug regulatory authorities as required.

Serious AEs refer to events that require hospitalization, prolonged hospital stay, disability (except for joint damage caused by rheumatoid arthritis), an inability to work (except for joint damage caused by rheumatoid arthritis), or which are life-threatening or can cause death during the clinical trial. Incidences of serious AEs among the patients will be promptly notified to the principal investigator by the researcher for appropriate course of action according to the study plan and the project’s standard operating procedure, and will be reported to the Good Clinical Practice office within 24 h and also to the relevant department. We will provide appropriate compensation for any injured subjects.

### Moral consideration

This trial has been approved by the Research Ethics Committee, the First Clinical Medical College of Guangzhou University of TCM, on 10 April 2019. All patients must sign an informed consent form before participating in the study.

### Quality assurance

The personnel participating in the clinical trial will be relatively permanent and will carefully study and discuss the clinical trial plan and manual, and unify the record method and judgment criteria. Researchers will use a pen or gel pen to fill in the CRF in a realistic, detailed, and serious manner. All observations and findings in the clinical trial will be verified to ensure reliability of data and to ensure that the conclusions from the trial are derived from raw data. There are corresponding data management measures in the clinical trial and data processing stages. Researchers will actively take measures to control the case drop-out rate to within 10%. In the event of a drop-out, the investigator should contact the participant, ask for reasons, record the last medication time, and complete the assessment project as far as possible. Laboratory data will be recorded in the CRF, and the original report will be attached with the medical record. Normal ranges of various laboratory parameters will also be recorded; data that is significantly higher or outside the clinically acceptable range will be verified and the necessary instructions will be provided by the physician participating in the clinical trial. The interventional drugs used in the clinical trial will be regularly inspected by the person responsible for administering the drug, and the status of the drug will be accurately recorded. Yishen Tongbi decoction is provided by the department of decoction of TCM in our hospital. Each batch of TCM decoction will be tested by high-performance liquid chromatography to ensure its compliance with quality requirements.

### Data management

The data monitoring committee is composed of the person in charge, data managers, data ombudsmen, and statistical analysts. Data from the CRF table will be entered into the ResMan database by the data administrator using two entry methods. The Ombudsman will check each item in the database, report inconsistent outcome values, and verify each item of the original questionnaire, and correct it if necessary. All research-related data will be kept in the Department of Rheumatology, the First Affiliated Hospital of Guangzhou University of TCM. The personal information of all the study participants will be kept strictly confidential.

### Sample size

A noninferiority test of Yishen Tongbi decoction and MTX will be adopted. The main efficacy end point is good response on the CDAI (improvement ≥50% or score ≤2.8) after 24 weeks. The study was designed to have a power of approximately 80% and a one-sided level of significance of 0.05 (α = 0.05, β = 0.2). The rate reaching the end point of the Yishen Tongbi decoction group was 68.0% from a previous study by our group, and the rate of the MTX group was 52.2% taken from the literature [7, 12]. The noninferiority margin was set to −0.10 [13]. The proportion of cases between the experimental and control groups was set to 1:1. The sample size for each group can be estimated as 45. Considering a drop-out rate of 10%, a total sample size of 100 participants is required. We used the calculation tool at https://www.cnstat.org/samplesize/.

### Statistical analyses

The efficacy of Yishen Tongbi decoction and MTX will be compared by a noninferiority test. We will conduct intention-to-treat and per-protocol analysis on the main results from the trial. The intention-to-treat analysis will analyse all eligible patients who have received at least one dose of medication. The per-protocol analysis will analyse all patients who meet the inclusion criteria and who do not meet the exclusion criteria and who complete the treatment plan. The proportion of subjects achieving good response on CDAI, SDAI and ACR in both groups will be compared. If the good response rate of CDAI in the Chinese medicine group is not lower than the good response rate of CDAI in the western medicine group by a margin of −0.1, it will be declared as noninferiority. The changes in CDAI, SDAI and Disease Activity Score in 28 joints from baseline after the corresponding treatment will be calculated and the results of the two groups will be compared using an independent sample analysis of covariance (ANCOVA). The amount of improvement of various ACR parameters (tender joint count, swollen joint count, visual analogue score, erythrocyte sedimentation rate, C-reactive protein, etc.) will be analysed and ANCOVA will be performed. For safety, the incidence of AEs in both the groups will be analysed and compared; the details of each AE will be analysed.

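### The set labelled intention-to-treat omits undosed randomised patients, the per-protocol set keeps only completers, and the non-inferiority rule names neither, so the conclusion can turn on which set is used

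*Protocol article*

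**What the plan says.** The Statistical analyses section commits to two analyses of the main results.

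- **Intention-to-treat:** "The intention-to-treat analysis will analyse all eligible patients who have received at least one dose of medication".
- **Per-protocol:** patients who satisfy the inclusion criteria, "who do not meet the exclusion criteria and who complete the treatment plan".

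One decision rule follows. Non-inferiority is declared if the CDAI good-response rate on decoction is not below the MTX rate by more than the 0.1 margin. The rule does not say which set it applies to, which set is primary, or whether both must agree.

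On timing, Randomization and blinding says "Unblinding will be carried out before the statistical analysis". It does not say when membership of the sets is settled.

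The Sample size section gives the design: "The study was designed to have a power of approximately 80" per cent, with "a one-sided level of significance of 0.05 (α = 0.05, β = 0.2"). It allows for 10% drop-out overall and does not split this by arm.

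**The concern.** Three features act together.

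1. A set restricted to dosed patients is a modified intention-to-treat set. The label promises the full randomised comparison and the definition does not deliver it.
2. Completing 24 weeks is a post-randomisation outcome. It can depend on lack of response or on toxicity, and these may differ between two active treatments. If more decoction patients with poor response stop early, removing them raises the decoction response rate among those who remain.
3. The rule that decides the trial is tied to no set. If the two analyses disagree, the protocol does not say which governs.

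What is at stake is the 5% one-sided error rate of the non-inferiority claim, and whether a reader can tell in advance what would count as success.

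**Working it through.** **Inputs from the Sample size section.** Decoction 68.0%, MTX 52.2%, margin -0.10, one-sided α = 0.05, power 80%, 45 per group, 10% drop-out, 100 in total.

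**Step 1. Reproduce the plan's own figure.** The distance from the margin is 0.680 - 0.522 + 0.10 = 0.258, and (1.645 + 0.842)² = 6.183.

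- Unpooled variance: (0.522×0.478 + 0.680×0.320) × 6.183 / 0.258² = 0.4671 × 6.183 / 0.06656 = 43.4, so 44 per group.
- Pooled variance, mean rate 0.601: 2×0.601×0.399 × 6.183 / 0.06656 = 44.5, so 45 per group, as stated.
- Drop-out: 45 / 0.90 = 50 per group, 100 in total, as stated.

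The sample size is reproduced, and the point does not depend on it.

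**Step 2. Can the choice of set reverse the conclusion?** The lower limit is d - 1.645 × √[p₁(1-p₁)/n₁ + p₂(1-p₂)/n₂]. Take 50 per arm, 28 decoction and 26 MTX responders, and 7 v 3 drop-outs (10 of 100, the planned overall rate).

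- All randomised, drop-outs as non-responders: 28/50 - 26/50 = +0.040; SE 0.0996; lower limit 0.040 - 1.645×0.0996 = -0.124. This fails.
- Completers: 28/43 - 26/47 = 0.651 - 0.553 = +0.098; SE 0.1027; lower limit 0.098 - 1.645×0.1027 = -0.071. This passes.

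The same patients give opposite conclusions.

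**Step 3. Error rate when the decoction is exactly at the margin.** Simulation with 50 per arm. True response among all randomised is 42.2% v 52.2%, so the difference is -0.10. Drop-outs are non-responders, so the response rate in completers is the all-randomised rate divided by (1 - drop-out). At 15% v 5% this is 0.422/0.85 - 0.522/0.95 = 0.496 - 0.549 = -0.053, so the completer comparison has moved about halfway from the margin to zero. The test is the lower limit of step 2 against -0.10.

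| Drop-out, decoction v MTX | All randomised | Completers | Either set | Both sets |
|---|---|---|---|---|
| 10% v 10% | 4.5% | 4.1% | 5.4% | 3.2% |
| 15% v 5% | 4.4% | 11.8% | 11.9% | 4.4% |
| 20% v 5% | 4.5% | 18.5% | 18.5% | 4.5% |
| 5% v 15% | 4.5% | 1.1% | 4.5% | 1.1% |

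**Step 4. Power at the planning rates.** With 68.0% v 52.2% among completers and 10% drop-out in each arm counted as non-response, power is 77% for all randomised, 81% for completers and 75% if both must pass.

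The drop-out splits and the handling of drop-outs as non-responders are assumptions. The protocol gives only the overall 10%. The simulation compares all randomised patients with completers; it does not model the exclusion of undosed or ineligible patients.

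**The case against.** A reader might infer three stronger things, and the protocol supports none of them.

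- **That patients judged ineligible are removed from the intention-to-treat set.** The Abstract and Study design call all 100 randomised patients eligible, and only the per-protocol sentence repeats the entry criteria. The word may simply mean enrolled. It is an ambiguity to settle.
- **That the sets are chosen after unblinding.** Randomization and blinding puts unblinding before the analysis, which is the usual order. Nothing plans a later choice of set, and an analysis plan that is not shown could freeze membership while blinded.
- **That success in either set is enough.** No such rule is written. Both analyses are promised, so a disagreement should be visible.

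Further, a completer per-protocol set beside an intention-to-treat set is conventional. Whether a patient took one dose is a fact rather than a judgement, and under double-dummy blinding it should be largely unrelated to arm. The inflated error needs more drop-out on decoction, and the protocol gives no reason to expect that direction. The 20% v 5% case averages 12.5%, above the 10% ceiling that Quality assurance aims for. Naming the deciding set is often left to the analysis plan, and requiring both sets is one accepted convention among others.

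All of this narrows the point without removing it. The intention-to-treat definition is printed and excludes undosed patients on any reading. The decision rule is printed and attached to no set. The 15% v 5% split and the 7 v 3 example both stay within the protocol's own 10% overall drop-out.

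**Conclusion.** The point holds in a limited form. The label and the definition of the intention-to-treat set do not agree, the meaning of eligible is open, and the non-inferiority rule does not identify the comparison that decides the trial.

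The size is conditional on drop-out being heavier on decoction and on drop-outs being non-responders. Under those assumptions the nominal 5% error becomes about 12% (15% v 5%) or 18.5% (20% v 5%) in completers or under an either-set reading. With equal drop-out it is 5.4% for either set, and with heavier drop-out on MTX it is 4.5%. Requiring both sets kept it at or below 4.5% in all four scenarios. These figures concern completers; the effect of omitting undosed patients was not measured and is probably small.

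This is a correction that should be made, because it is cheap and settles in advance a result that can otherwise go either way. It does not show that the sponsor intends to select a set.

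**What to change.** 1. In Statistical analyses, define intention-to-treat as all randomised patients in their assigned group, and count a missing week-24 CDAI as non-response.
2. In the same section, declare non-inferiority only if the one-sided 95% lower confidence limit for decoction minus MTX exceeds -0.10 in both the intention-to-treat and the per-protocol set.
3. In Randomization and blinding, state that set membership and the database are fixed before unblinding. The current text leaves this open and does not contradict it.

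The cost is wording plus a restated power. At the planning rates with 10% drop-out per arm, power is about 75% when both sets must pass (77% for intention-to-treat alone) against the stated 80%. The Sample size section should say so.

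### The primary noninferiority comparison names no covariate adjustment; a pre-specified adjusted risk difference may gain some precision at no cost in patients

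*Protocol article*

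**What the plan says.** Protocol article, Statistical analyses: for the responder endpoints, "The proportion of subjects achieving good response on CDAI, SDAI and ACR in both groups will be compared". Noninferiority is declared if the CDAI good-response rate on the decoction falls below the MTX rate by no more than 0.1. No test, interval method, model or covariate is named for this comparison, and the text does not say whether it is adjusted. In the same section, changes in CDAI, SDAI and DAS28 "will be compared using an independent sample analysis of covariance (ANCOVA"), and ANCOVA is named again for the ACR components. The covariates for those analyses are not listed either.

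Sample size: "The study was designed to have a power of approximately 80% and a one-sided level of significance of 0.05". The planning rates are 68.0% on the decoction and, for the control, "the rate of the MTX group was 52.2% taken from the literature". "The noninferiority margin was set to −0.10". This leads to 45 per group, and to 100 in total after allowing for 10% drop-out.

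Randomization and blinding: 25 blocks of four, with no stratification factor named. Unblinding comes before the statistical analysis.

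Interventions: "Treatment can be maintained if the patient has taken a steady dose of a corticosteroid" or an NSAID before the trial. Medication is entered in the case report form at follow-up visits.

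Outcomes and measurements: disease activity is assessed at baseline and at weeks 4, 12 and 24. The primary endpoint is at least 50% improvement in CDAI, or CDAI of 2.8 or less, at week 24.

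**The concern.** The trial is small, and its noninferiority claim rests on one binary comparison with power close to 80%. Blocks of four keep the arms equal in size but do not balance disease activity or background corticosteroid use. The article plans a covariate method for the continuous scores, which do not decide the trial, and names none for the comparison that does. If baseline covariates predict response, adjusting for them narrows the confidence interval that is set against −0.10 without recruiting anyone else. At stake is a modest amount of power, not the validity of the result.

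**Working it through.** **Inputs.** From Sample size: p_T = 0.680, p_C = 0.522, margin 0.10, one-sided α = 0.05 (z = 1.645), power 80% (z = 0.842), 1:1 allocation, 45 per arm before drop-out. Assumed, because the documents give no figure: R², the share of the variance in response explained by baseline covariates.

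**1. Reproduce the stated size.**
- Distance from the margin: 0.680 − 0.522 + 0.10 = 0.258.
- Unpooled variance: 0.680 × 0.320 + 0.522 × 0.478 = 0.2176 + 0.2495 = 0.4671.
- n = 0.4671 × (1.645 + 0.842)² / 0.258² = 43.4, so 44 per arm.
- With pooled variance (mean rate 0.601): n = 2 × 0.601 × 0.399 × (1.645 + 0.842)² / 0.258² = 44.5, so 45 per arm.
- 45 / 0.90 = 50 per arm, 100 in total.

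The stated size is reproduced by a two-proportion formula without adjustment.

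**2. Power with and without adjustment, 45 per arm.** Adjustment is approximated by multiplying the variance by (1 − R²):

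Power = Φ[0.258 / √(0.4671 × (1 − R²) / 45) − 1.645]

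| Assumed R² | Effective n per arm, 45/(1 − R²) | SE of difference | Power |
|---|---|---|---|
| 0 | 45 | 0.102 | 81.3% |
| 0.05 | 47.4 | 0.099 | 83.0% |
| 0.10 | 50.0 | 0.097 | 84.7% |
| 0.15 | 52.9 | 0.094 | 86.5% |

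**3. Simulation check.** 4,000 trials per scenario, 45 per arm, one normally distributed baseline covariate. The raw risk difference was compared with a logistic model standardised to a risk difference, both tested one-sided at 5% against −0.10.

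| Covariate effect (log-odds per SD) | Power at 68.0% v 52.2%: raw / adjusted | Type I error with the true difference at −0.10: raw / adjusted |
|---|---|---|
| 0 | 79.8% / 80.0% | 4.5% / 4.8% |
| 0.5 | 79.2% / 81.6% | 4.9% / 5.2% |
| 1.0 | 81.1% / 87.1% | 4.3% / 4.9% |

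At the planning rates, adjustment reduced the variance of the estimate by 3% with the moderate covariate and 16% with the strong one. With a covariate of no value the variance rose by about 1%, and power was unchanged. Both methods hold the nominal 5% within simulation error.

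**4. If the arms are in fact equal.** With both rates at 52.2%, the variance is 2 × 0.522 × 0.478 = 0.499 and power is Φ[0.10 / √(0.499 / 45) − 1.645] = 24%. With R² of 0.10 to 0.30 it is 26 to 31%.

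**The case against.** The strongest reply is that nothing here is wrong. An unadjusted comparison of randomised arms is valid, and it matches the formula used to size the trial. Chance imbalance is already reflected in its standard error. That stands in full: the simulated type I error of the raw comparison was 4.3 to 4.9% at a nominal 5%. A reader might infer that the lack of stratification and the allowance for background corticosteroids bias the primary result, so that adjustment would remove the bias. The documents do not support this. Adjustment here would improve precision; it would not correct a bias. Nor would a model with baseline CDAI and corticosteroid use deal with imbalance in NSAID use, which it does not contain.

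Second, the article never says that the comparison is unadjusted. The plain-rate decision rule and the sizing formula point that way, but a sizing formula does not fix the analysis model, and an analysis plan that is not shown may name covariates. If it does, the point is met.

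Third, the contrast with ANCOVA is loose. Using ANCOVA for continuous change and a rate comparison for responders is ordinary practice, not a contradiction. The primary endpoint is mostly a percentage change from baseline CDAI, so baseline CDAI may predict it less well than it predicts a continuous score. The documents offer no evidence either way.

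Fourth, recording of corticosteroid use at baseline is implied by the eligibility and concomitant-medication text but not stated, and the number of users is unknown.

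What survives is narrower. The decisive comparison is described without adjustment, baseline CDAI is collected, and using it costs almost nothing when it is uninformative and helps when it is not.

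**Conclusion.** The point holds as an optional improvement of low severity. As described, the primary comparison is sound but may leave some precision unused. The size rests on an R² that the documents do not give: no gain at R² = 0, and about 2 to 5 power points at an assumed R² of 5 to 15% (81% to about 83 to 86%), all at the planning rates of 68.0% and 52.2% with 45 evaluable per arm. A reader might also hope that adjustment would protect the trial if the decoction were merely equal to MTX. It would not: power stays at or below about 31% in that case, even at an assumed R² of 0.30.

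**What to change.** Before unblinding, add to the analysis plan:

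- **Primary estimate:** the marginal risk difference in CDAI good response at week 24, obtained by standardisation (g-computation) from a logistic model with treatment and baseline CDAI. Add baseline corticosteroid use (yes/no) if it is recorded at baseline.
- **Decision rule:** the lower one-sided 95% confidence limit of that difference (delta method or bootstrap) compared with −0.10. An adjusted odds ratio should not replace it, because the margin is set on the difference in rates.
- **Sensitivity analysis:** the unadjusted difference with its interval, reported alongside.

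The choice should be fixed before unblinding because covariates chosen afterwards would look data-driven. The cost is a few lines of text and code, with no extra patients. Baseline CDAI needs no new data; for corticosteroid use, check that the case report form captures it at baseline.
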